### Definitions

Day 0 of invasive ventilation is defined as the day respiratory support is started in the participating ICU; in the initial phase, this is the day at which invasive ventilation is started. Day 1 is defined as the first full calendar day, with Day 2 and Day 3 representing the two consecutive mornings that follow. Pediatric acute respiratory distress syndrome is defined according to the 2023 Pediatric Acute Lung Injury Consensus Conference (PALICC-2) definition.^(23)^ Intensive care unit length of stay is defined as the time between ICU admission and discharge or death; duration of respiratory support, in the initial phase invasive ventilation, is defined as the time between initiation and successful liberation. Intensive care unit mortality is defined as any death until ICU discharge or day 28, whichever comes first.

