### Data collection

All data to be collected are part of standard clinical care. Throughout each phase of the study, the data collected will be tailored to align with the evolving focus of the research, ensuring that it remains relevant and reflects the specific objectives of each stage. At admission, we will collect data on patient demographics - including age, gestational age, sex, height and weight, comorbidities, and baseline characteristics - including reasons for intensive care unit (ICU) admission, and the start of respiratory support, presence of the pediatric acute respiratory distress syndrome (PARDS), and disease severity scores. For 4 days, beginning with the day of start of respiratory support, daily data will be collected at a time in the morning - including data on respiratory support and the respiratory status. Follow-up will be until day 28 to collect outcome data, including the date of stop of respiratory support, date of ICU discharge, and life status at ICU discharge or at day 28, whichever comes first.

Investigators will transcribe all collected data into a web-based electronic Case Report Form (eCRF) (Castor Electronic Data Capture, Amsterdam, the Netherlands).^(22)^ The eCRF complies with all applicable laws and regulations. Transcription will only take place in a secure environment. Directly identifying personal data will be separated from the research data and replaced by an assigned code. The directly identifying data will only be used to contact the patients and will only be available to the local investigators. Access to the assigned codes linked with personal data will be password-protected, restricting access to only the data directly related to the local investigator.

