### Study endpoints

The study endpoints vary based on the study's evolving scope. Since the scope of the initial phase of PRoVENT-PED is invasive ventilation, key endpoints include a set of ventilator settings and ventilation parameters, such as tidal volume (V_T_); maximum (Pmax), peak (Ppeak), plateau (Pplat) and mean airway pressures (Pmean); positive end-expiratory pressure (PEEP); fraction of inspired oxygen (FiO^2^); and respiratory rate (RR) at fixed time points over the first four days of invasive ventilation. Driving pressure (ΔP), respiratory system compliance (C_RS_), and measures of ventilation intensity are calculated daily from these data. Other endpoints include duration of ventilation in survivors and nonsurvivors, the number of days free from invasive ventilation and alive at day 28, length of stay in ICU and hospital, and mortality rates in ICU and hospital and at day 28.

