### Calculations

Ventilator-free days at day 28 (VFD-28) is calculated as 28 minus the number of days a subject was successfully liberated from ventilation after initiation. If a patient dies within 28 days, VFD-28 will be recorded as zero. The V^T^ is normalized to actual body weight (ABW), and ΔP,^(8)^ C_RS_,^(24)^ mechanical power (MP)^(25)^ and mechanical energy (ME) of ventilation,^(26)^ are calculated using the following equations 1 to 9:

[Equation 1]
$${\text{V}}_{\text{T}}\text{normalized to ABW}={\text{V}}_{\text{T}}/\text{ABW}$$

[Equation 2]
ΔP=Pplat−PEEP in volume-controlled ventilation (VCV)

[Equation 3]
ΔP=Pmax−PEEP in pressure-controlled ventilation(PCV)

[Equation 4]
$${\text{C}}_{\text{RS}}={\text{V}}_{\text{T}}/(\text{Pplat}-\text{PEEP})(\text{with VCV})$$

[Equation 5]
$${\text{C}}_{\text{RS}}={\text{V}}_{\text{T}}/(\text{Pmax}-\text{PEEP})\text{(with PCV)}$$

[Equation 6]
$$\text{MP}=0.098^{*}\;{\text{V}}_{\text{T}}*\text{RR}*(\text{Ppeak}-0.5^{*}\Delta \text{P})(\text{with VCV})$$

[Equation 7]
$$\text{MP}=0.098^{*}\;{\text{V}}_{\text{T}}*\text{RR}*(\mathrm{Pmax}-0.5^{*}\Delta \text{P})(\text{with PCV})$$

[Equation 8]
$$\text{ME}=0.098^{*}\;{\text{V}}_{\text{T}}/{\text{kg}}^{*}(\text{Ppeak}-0.5^{*}\Delta \text{P})$$

[Equation 9]
$$\text{ME}=0.098^{*}{\text{V}}_{\text{T}}/{\text{kg}}^{*}(\mathrm{Pmax}-0.5^{*}\Delta \text{P})$$

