### Statistical analysis

Descriptive statistics will be used to describe patient demographics and baseline characteristics, types of respiratory support used, device settings, and respiratory variables and parameters, including measures of oxygenation and decarboxylation. Continuous variables will be expressed in medians and interquartile ranges, and categorical variables will be expressed in frequencies and proportions. The Kruskal-Wallis test will be used to compare continuous variables, and the Chi-squared test will be used for categorical variables.

Respiratory support settings and respiratory variables and parameters at successive days will be reported in detail for the first days of respiratory care and compared between different age groups, i.e., neonates (< 1 month), infants (1 month to < 12 months), toddlers (12 months to < 3 years), preschoolers (3 years to < 6 years), school-age children (6 years to < 12 years), and adolescents (12 years to 18 years). Additionally, respiratory support settings, respiratory variables, and ventilation parameters will be compared between patients with and without PARDS and across other patient groups, including patients receiving respiratory support due to a pulmonary disease *versus* non-pulmonary conditions and patients receiving ECMO.

Key respiratory support settings, respiratory variables, and parameters will be visualized using cumulative distribution plots for the first days and line graphs over successive days. Inpatient trends over time are assessed with mixed-effect linear models with patients treated as a random effect to account for clustering and repeated measurements, and with day, different patient group and their interaction as fixed effects. P values from this analysis represent the overall difference among different patient groups over time, and p values from interaction represent the difference in trend over time among the different patient groups.

Time-to-event outcomes, like liberation from the ventilator, discharge and death, will be presented in Kaplan-Meier curves. Cox proportional hazard modelling or competing risk analyses will be used to study associations with continuous clinical outcomes, presented as hazard ratios (HR) and 95% confidence intervals (95%CIs). Logistic regression will be used to study the association between key ventilator settings and ventilation parameters and binary clinical outcomes, and will be presented as odds ratios (OR) and 95%CIs.

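### Duration of ventilation is defined to end only at successful liberation, so the nonsurvivor endpoint has no value for a child who dies while ventilated

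*Protocol article*

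**What the plan says.** All references are to the protocol article.

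- Study endpoints: "Other endpoints include duration of ventilation in survivors and nonsurvivors". Nonsurvivors are therefore a group for which a figure will be reported.
- Definitions: duration of respiratory support, which in the initial phase means invasive ventilation, "is defined as the time between initiation and successful liberation". No other end is given.
- Definitions, in the same sentence: "Intensive care unit length of stay is defined as the time between ICU admission and discharge or death". Here death is an explicit end.
- Data collection: "Follow-up will be until day 28 to collect outcome data". The items recorded cover when support ended, when the child left the ICU, and whether the child was alive at that point or at day 28.
- Calculations: "If a patient dies within 28 days, VFD-28 will be recorded as zero".
- Statistical analysis: "Time-to-event outcomes, like liberation from the ventilator, discharge and death, will be presented in Kaplan-Meier curves". Associations are then to be studied with either Cox models or competing-risk analyses, and the choice is left open.

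**The concern.** The definition does not fit the endpoint it serves. Death on the ventilator is one of the main ways in which ventilation ends for a nonsurvivor, and the definition has no place for it. Applied to the letter, it restricts the nonsurvivor figure to children who came off the ventilator and died afterwards, and they may differ from those who died ventilated. Children still ventilated at day 28 also fall outside it, and theirs are the longest courses observed.

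Two things are at stake. First, the nonsurvivor figure may describe a different group from the one its label suggests. Second, in an international study some centres or analysts may apply the definition literally while others enter the date of death as the end, so the same course could be recorded in two ways. That matters for the planned comparisons by age group, PARDS status and other patient groups, where mortality may differ.

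**Working it through.** The plan states no figure on this point, so there is nothing to reproduce. The check is to apply the definition to each possible course and then look for a repairing rule elsewhere.

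**Step 1. Apply the definition.**

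| Course | Value under Definitions |
|---|---|
| Liberated, survives | Defined |
| Liberated, dies later | Defined |
| Dies while ventilated | None |
| Still ventilated at day 28 | None |

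**Step 2. Look for a rule elsewhere.**

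- The zero rule for deaths in Calculations covers ventilator-free days only, which is a separate endpoint.
- The date on which support stops is collected and could serve as the end date for a child who dies ventilated. The definition does not use it.
- Kaplan-Meier curves and Cox or competing-risk models deal with time to liberation. None of them says what duration to summarise for a nonsurvivor.
- Results reports a pilot median duration of 4 [2 - 10] days without saying how the deaths were counted, so the pilot does not reveal a working rule.

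**Step 3. Scale, for orientation only.** Inputs: 3,000 patients and 3% ICU mortality (Sample size calculation); 10 deaths in 125 pilot patients (Results, Table 1).

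- Pilot mortality: 10 / 125 = 8%.
- Deaths at 3%: 3,000 × 0.03 = 90.
- Deaths at 8%: 3,000 × 0.08 = 240, if all 3,000 are enrolled. The Discussion allows the phase to end sooner if mortality is high. The target of 100 deaths would then be met at 100 / 0.08 = 1,250 patients.

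The share of deaths that occur on the ventilator is not given. Taking 50% to 100% as an assumption, the number of children who die with no defined duration is:

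- at 3%: 45 to 90;
- at 8% with 3,000 enrolled: 120 to 240.

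**Step 4. Effect on the survivor median.** Among survivors, only children still ventilated at day 28 lack a value. In the pilot, 125 − 106 discharged − 10 dead = 9, if discharges and deaths do not overlap. Suppose all 9 were ventilated at day 28 and were dropped from the top of the 115 survivors. The reported median would then sit at 0.5 × 106 / 115 = 0.46, the 46th percentile of the full group. On that assumption the shift is small.

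**The case against.** The best defence is that the intent is plain. The article asks for duration in nonsurvivors and collects the date support stops, so a sensible analyst would use that date for a child who dies ventilated, and no data are lost. The survivor/nonsurvivor split is already planned, competing-risk analysis is already named, and medians with interquartile ranges are not very sensitive to a few long courses. An operational rule may also stand in the case report form or in an analysis plan that is not shown.

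Much of this stands, and it keeps the point small. It does not remove it. The article does not leave the definition to another document: it states one, and that one fails for its own endpoint, while the same sentence handles death correctly for ICU stay.

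A reader might infer three stronger things that the documents do not support.

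- *That overall duration is biased downward.* Dropping children ventilated at day 28 lowers the figure, but dropping early deaths, which have short courses, raises it. The timing of deaths is not given, so the net direction is unknown.
- *That only a minority of nonsurvivors would have a value.* No section says how many were liberated before death.
- *That up to 15% of patients lack a value*, from (10 + 9) / 125 = 15.2% in the pilot. This is neither an estimate nor an upper bound. Some of the 10 and some of the 9 may have been liberated, while the 5 children discharged to another hospital's ICU may still have been ventilated.

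**Conclusion.** The point holds. The stated definition of duration of ventilation gives no value to a child who dies while ventilated, although duration in nonsurvivors is a listed endpoint, and none to a child still ventilated at day 28. This follows from the wording alone and needs no numerical assumption. How many children are affected cannot be derived from the documents. The 90 or 240 deaths show scale only, and the ranges in the working rest on an assumed share dying ventilated.

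The consequence is limited. This is one of the other endpoints, it does not enter the sample size calculation, and the damage arises only if the definition is applied as written. It is worth correcting because the correction is almost free.

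**What to change.** 1. In Definitions, let duration of ventilation run from initiation to the first of successful liberation or death while ventilated, with children still ventilated at day 28 censored there.
2. Keep the reporting by survivors and nonsurvivors already listed under Study endpoints.
3. In Statistical analysis, commit to the competing-risk option for time to liberation: present cumulative incidence with death as a competing event in place of a Kaplan-Meier curve. Kaplan-Meier with deaths censored treats a child who has died as one who could still be liberated, and so overstates the probability of liberation.

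The cost is one sentence in Definitions and a small edit in Statistical analysis. No new data are needed: the stop date and life status are already collected, and the existing definition of ICU stay already requires the date of death. The sample size does not change.

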### Calculations

Ventilator-free days at day 28 (VFD-28) is calculated as 28 minus the number of days a subject was successfully liberated from ventilation after initiation. If a patient dies within 28 days, VFD-28 will be recorded as zero. The V^T^ is normalized to actual body weight (ABW), and ΔP,^(8)^ C_RS_,^(24)^ mechanical power (MP)^(25)^ and mechanical energy (ME) of ventilation,^(26)^ are calculated using the following equations 1 to 9:

[Equation 1]
$${\text{V}}_{\text{T}}\text{normalized to ABW}={\text{V}}_{\text{T}}/\text{ABW}$$

[Equation 2]
ΔP=Pplat−PEEP in volume-controlled ventilation (VCV)

[Equation 3]
ΔP=Pmax−PEEP in pressure-controlled ventilation(PCV)

[Equation 4]
$${\text{C}}_{\text{RS}}={\text{V}}_{\text{T}}/(\text{Pplat}-\text{PEEP})(\text{with VCV})$$

[Equation 5]
$${\text{C}}_{\text{RS}}={\text{V}}_{\text{T}}/(\text{Pmax}-\text{PEEP})\text{(with PCV)}$$

[Equation 6]
$$\text{MP}=0.098^{*}\;{\text{V}}_{\text{T}}*\text{RR}*(\text{Ppeak}-0.5^{*}\Delta \text{P})(\text{with VCV})$$

[Equation 7]
$$\text{MP}=0.098^{*}\;{\text{V}}_{\text{T}}*\text{RR}*(\mathrm{Pmax}-0.5^{*}\Delta \text{P})(\text{with PCV})$$

[Equation 8]
$$\text{ME}=0.098^{*}\;{\text{V}}_{\text{T}}/{\text{kg}}^{*}(\text{Ppeak}-0.5^{*}\Delta \text{P})$$

[Equation 9]
$$\text{ME}=0.098^{*}{\text{V}}_{\text{T}}/{\text{kg}}^{*}(\mathrm{Pmax}-0.5^{*}\Delta \text{P})$$

### Sample size calculation

The sample size will vary across each phase. In the initial phase, which focuses on invasive ventilation, the sample size calculation is based on identifying potentially modifiable factors independently associated with ICU mortality. We plan to include up to ten modifiable factors in the model to achieve this. Using logistic regression and the rule of thumb of ten events per factor, we estimated a need for one hundred events’, that is ICU deaths. Based on a conservative ICU mortality rate estimate of 3%,^(1,27)^ 3,000 patients will be required. However, depending on the actual mortality rate observed with each 4-week interval, the sample size may be adjusted accordingly. For subsequent phases, in which the study's focus and analysis plan will shift, sample sizes will be recalculated and reported in the study amendment and on Clinicaltrials.gov.

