A robust locally weighted scatter plot smoothing (LOWESS) method will be used to investigate the association between ICU mortality and key ventilatory variables and parameters, including V^T^, Ppeak, PEEP, FiO^2^, RR, PaO^2^/FiO^2^, ΔP, MP and ME. The smoothing curves will be generated with a bandwidth of 0.66, a polynomial regression with 1 degree of freedom, and a tricubic weighting function so that observations furthest from the point of interest are assigned the least weight.

In a univariate analysis, the impact of the single key ventilatory variables on mortality will be assessed by estimating the relative risk of all-cause 28-day ICU mortality. Multivariate logistic regression will be used for the adjusted analysis, adjusting for unequal distribution of effect modifiers. We will adjust for baseline covariates selected according to clinical relevance, including age, sex, weight, comorbidities, and severity of illness. Results will be shown as ORs with 95%CI. Multiple imputation will be performed to account for missing values.

Data will be analyzed with R version 4.2.2 (R Core Team, 2022, Vienna, Austria). Statistical uncertainty will be expressed by 95%CIs. A p value < 0.05 is considered statistically significant.

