The sample size for PRoVENT-PED will be adapted across the different phases of the study. In the initial phase, which focuses on invasive ventilation, the sample size calculation is designed to identify potentially modifiable factors independently associated with ICU mortality. However, the sample size may be adjusted based on the observed mortality rates during this inclusion period. In the pilot feasibility study, mortality was higher than predicted in the initial sample size calculation. If this finding is confirmed in the early periods of the study, it may allow for an earlier conclusion of the initial phase, as the required number of events would be reached sooner than anticipated. This adaptive design is a key strength of PRoVENT-PED, as it aligns recruitment efforts with observed clinical outcomes, minimizing unnecessary workload and ensuring efficient use of resources.

Ventilation practices in adult and pediatric ICUs continuously evolve, driven by emerging evidence and external factors such as pandemics. In adult patients, the adoption of HFNO has increased steadily, supported by positive findings across diverse clinical settings,^(47-53)^ including in the COVID-19 pandemic.^(14,54)^ Awake-prone positioning also became more prevalent^(55)^ while reliance on high PEEP strategies decreased.^(56-58)^ Similarly, pediatric ICUs have embraced noninvasive strategies with growing frequency,^(59-61)^ particularly HFNO, although evidence of benefit is lacking.^(43,45,46,62,63)^ The COVID-19 pandemic also influenced the epidemiology of pediatric respiratory infections, leading to fewer pediatric ICU admissions in 2020 and 2021, followed by a resurgence with greater severity and increased ventilatory support requirements.^(64-71)^ These evolving trends highlight the importance of ongoing research into respiratory support practices. A notable strength of PRoVENT-PED is its capacity to incorporate additional data collection during epidemics or pandemics, facilitating more timely and relevant insights.

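### The stated 3,000 patients give 90 expected deaths, not the 100 required, and the 100-death target leaves out the covariates in the adjusted model

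*Protocol article*

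**What the plan says.** The initial phase is sized on a logistic model for ICU mortality. The Sample size calculation section states: "We plan to include up to ten modifiable factors in the model to achieve this". It continues "Using logistic regression and the rule of thumb of ten events per factor", and from this "we estimated a need for one hundred events", meaning ICU deaths. The mortality input is introduced with "Based on a conservative ICU mortality rate estimate of 3" per cent, and the conclusion is that "3,000 patients will be required". The section adds that "depending on the actual mortality rate observed with each 4-week interval, the sample size may be adjusted accordingly".

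The Statistical analysis section describes the adjusted multivariable logistic model: "We will adjust for baseline covariates selected according to clinical relevance, including age, sex, weight, comorbidities, and severity of illness".

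The Discussion reports that pilot mortality was above the planning value and says that, if this is confirmed, "it may allow for an earlier conclusion of the initial phase, as the required number of events would be reached sooner than anticipated". It also says that the study moves on to its next topic once the sample size needed for the current one has been reached.

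**The concern.** Two things do not fit together.

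First, the stated sample size does not follow from its own inputs. The gap runs in the unfavourable direction: the stated number of patients is too small for the stated number of deaths.

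Second, the event rule is applied to a smaller model than the one described. The 100 deaths are ten times the maximum number of modifiable factors, with nothing allowed for the adjustment covariates. Yet the aim is to find factors with an independent association, so the covariates belong in the model and use up events as the factors do.

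What is at stake is the precision and stability of the adjusted odds ratios, and the basis for deciding when the initial phase has enough deaths. If the target is too low for the model, adapting the sample size to that target carries the shortfall forward.

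**Working it through.** **Inputs**
- Modifiable factors: up to 10 (Sample size calculation)
- Events per factor: 10 (same section)
- ICU mortality: 3% (same section)
- Stated sample size: 3,000 (same section)
- Named covariates: severity, comorbidities, weight, sex and age, so at least 5 (Statistical analysis)
- Pilot 28-day ICU mortality: 8%, 10 of 125 (Results and Table 1); used only for sensitivity

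**Step 1. The plan's own figure**
- Required deaths = 10 × 10 = 100. This reproduces the plan's event target.
- Required patients = 100 / 0.03 = 3,333.3, rounded up to 3,334. The stated 3,000 is not reproduced.
- Shortfall = 3,334 − 3,000 = 334 patients, about 10% of the number needed (334 / 3,334).
- Expected deaths in 3,000 patients = 3,000 × 0.03 = 90.
- 3,000 would be right only with a mortality of 100 / 3,000 = 3.33%, or with a target of 90 deaths. The article states neither. Any allowance for loss to follow-up would raise the number, not lower it.
- If enrolment stopped at exactly 3,000 and true mortality were exactly 3%, the binomial probability of at least 100 deaths would be about 0.15.

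**Step 2. Events per parameter in the described model**

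Parameters = 10 factors + 5 covariates at one parameter each = 15. Events per parameter = deaths / parameters.

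| Deaths | 10 factors alone | 15 parameters |
|---|---|---|
| 90 (3,000 patients at 3%) | 9.0 | 6.0 |
| 100 (the stated target) | 10.0 | 6.7 |

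The rule of ten is met only in the cell with 100 deaths and no covariates.

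**Step 3. Does adapting the sample size help?**
- If the phase runs until 100 deaths, the Step 1 gap closes, because the number of patients follows the deaths.
- Step 2 is unchanged: 100 / 15 = 6.7 whatever the mortality. At the pilot rate, 100 deaths arrive at 100 / 0.08 = 1,250 patients, still with 6.7 per parameter.
- If 3,000 patients were enrolled regardless, 15 parameters would have 120 / 15 = 8.0 at 4% mortality, 150 / 15 = 10.0 at 5% and 240 / 15 = 16.0 at 8%. Stopping early on deaths gives up that margin.

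**Step 4. What the rule implies once covariates count**
- At 100 deaths: 100 / 10 = 10 parameters in total, so 5 factors beside 5 covariates.
- At 90 deaths: 9 parameters in total, so 4 factors beside 5 covariates.
- Keeping 10 factors and 5 covariates: 15 × 10 = 150 deaths, which is 5,000 patients at 3% (150 / 0.03) or 1,875 at 8% (150 / 0.08).

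**The case against.** The best defence is that 3,000 is a planning figure and not a stopping point. The article calls 3% conservative, lets the number of patients change with observed mortality, and ties an early close to the number of deaths. On that reading the 90-versus-100 gap is a rounding slip that corrects itself. This largely stands for the consequences of the first part. The figure itself is still wrong on its inputs, and the article also speaks of moving on once the required sample size is reached. The defence does not help the second part, because the death target is what is set too low.

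A second defence is that ten is a ceiling on the number of factors. With five or fewer factors beside five single-parameter covariates, 100 deaths would meet the rule. That is correct, but the 100 deaths were derived from the full ten.

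A third is that the mortality model is not the whole study. The key endpoints of the initial phase are ventilator settings and ventilation parameters, and their description does not depend on events per parameter. This stands and limits the reach of the point.

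A reader might also infer more than the article supports:
- **That the model has six or fewer events per parameter.** This needs a hard stop at 3,000 with mortality no higher than 3%, all ten factors in use and at least 15 parameters. At the stated target the 15-parameter figure is 6.7.
- **That the model has 22 parameters.** This would enter each of the eight medical-history rows of Table 1 as a separate term. The article does not say how comorbidities are coded.
- **That the model is unidentifiable because driving pressure, mechanical power and mechanical energy sit beside their components.** No section puts them in one model. The list that names them belongs to the LOWESS curves and contains Ppeak, not Pmax. Mechanical power and energy are products of their components, so they may be strongly correlated with them but are not linear combinations of them.

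Only a caution remains from the last item. In pressure-controlled ventilation, Equation 3 makes driving pressure exactly Pmax minus PEEP, so those three should not all enter one model.

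**Conclusion.** The point holds in two parts.

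The sample size figure is wrong as written: it is 334 patients short of its own inputs, or equivalently 10 deaths short. This rests on nothing beyond the stated 100 deaths and 3%.

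The event target does not meet the plan's own rule for the adjusted model if all ten factors are used. The ratio is 6.0 per parameter at 90 deaths and 6.7 at 100, and closing the phase at 100 deaths fixes it at the latter. This assumes one parameter for each of the five named covariates. Any covariate that takes more than one parameter lowers the ratio, and fewer factors raise it.

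The yardstick here is the article's own rule of ten; no claim is made that ten is the correct threshold. The conclusion concerns the adjusted mortality model, not the descriptive aims of the initial phase.

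**What to change.** 1. Restate the figure as 3,334 patients for 100 deaths at 3%, or as 3,000 patients for 90 expected deaths. The second choice supports nine parameters under the rule, so the ceiling of ten factors would have to change with it.
2. State that the event rule counts every parameter in the adjusted model, covariates included.
3. Then choose one of two routes. Either limit factors plus covariates to what the deaths support (ten parameters in total at 100 deaths), or keep the larger model, drop the ten-per-factor claim for it and name a method suited to fewer events, such as a penalised fit.
4. Apply the same event rule when the sample size is adapted to observed mortality, so that an early close is judged against the full model.
5. As a precaution, note that Pmax, PEEP and driving pressure will not all be entered together for pressure-controlled ventilation.

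The cost is a corrected number and a few sentences. No patients are needed beyond the 100-death target if the model is kept to ten parameters. The downside is fewer factors per model, or a less favourable stated ratio. Keeping both ten factors and the rule of ten would instead need the 150 deaths shown in the working.
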